#### Inclusion and Exclusion Criteria

Participants in this study are required to be adults aged 18 or above and will be recruited after providing consent. Age verification will be based on their ID cards. Potential respondents may either be healthy or have various physical disabilities and demonstrate a willingness to participate. Additionally, they must be able to communicate in the Malay language. However, people with cognitive impairments will be excluded from the study.

#### Tools and Instruments

This study will comprise 3 evaluations: health literacy, health, and socioeconomic status. There are 8 parts to the questionnaire, which are outlined in Table 4.

**Table 4 table4:** Components of the questionnaire.

Component	Description
Part 1: Housing and the environment (head of household only)	Part 1 will capture family structure, household transportation, and water supply.
Part 2: Household income (head of household only)	Part 2 will record the household's annual income from all sources.
Part 3: Sociodemographic characteristics (all household members, including the head of household)	Part 3 will capture sociodemographic information such as date of birth, ethnicity, education, employment status, relationship status, and so on.
Part 4: Health care expenditure and utilization (all household members, including the head of household)	Part 4 questions will capture data on health payments, health care service utilization, traditional and complementary medicine practice, and health care expenditure.
Part 5: Modifiable lifestyle factors (all household members, including the head of household)	Part 5 will ask about tobacco consumption, nutrition, physical activity, and medical conditions.
Part 6: Medical information (all household members, including the head of household)	Part 6 will measure the height, weight, waist circumference, and hip circumference. The calibrated vertical SECA portable 217 stadiometer (SECA GmBH & Co KG) will be used to measure respondents’ height, the calibrated SECA 813 digital electronic weighing scale will measure weight, and the SECA 201 ergonomic measuring tape will measure waist (abdominal) and hip circumferences.
Part 7: Quality of life (all household members, including the head of household)	Questions in part 7 will assess the participant's quality of life using standard and generic methods.
Part 8: Health literacy status	Health literacy status will be determined using the HLS-SF-Q12^a^ [24]. The perceived difficulty of each health-related task is rated on a 4-point Likert scale (1=*very difficult*, 2=*difficult*, 3=*easy*, and 4=*very easy*), with a possible lowest mean score of 1 and a possible highest mean score of 4. The questions consider the 4 competencies of an individual when dealing with health-relevant information (access/obtain, understand, appraise/judge/evaluate, and apply/use health information) to form a judgment and make health-related decisions for the 3 domains of health care, disease prevention, and health promotion.

^a^HLS-SF-Q12: 12-item Short-Form Health Literacy Questionnaire.

#### Reliability, Validity, and Trustworthiness

Reliability indicates whether the results can be consistently reproduced or not. In this study, internal consistency is evaluated through the Cronbach α value, with a threshold set at greater than or equal to .70 for satisfactory reliability. At the same time, validity will measure the validity and accuracy of the questionnaire. Face and content validity will be used to measure the validity of the questionnaire. Notably, this study incorporates established questionnaires with preestablished reliability and validity from different sources [22,25].

#### Data Collection Procedure

A total of 8 interviewers will be required to conduct the survey, working in pairs. For security and dialect reasons, a local representative will be appointed to accompany each team. Before the data collection, the ground staff will introduce the interviewers to the household members to ensure that the head of the household and other members are present and grant permission for the interviewers to enter their personal premises. Once approval is obtained, the interviewer will explain the nature of the study based on the participants’ information sheet, which outlines the key details. Subsequently, the information sheet will be provided to the participants for their reference. In addition, the interviewers will reassure the participants that the information provided in the study will remain confidential and their participation is entirely voluntary. The face-to-face interview will begin shortly after the head of the household and other household members have signed the consent form. During the interview, the respondents’ height and weight will be measured, contingent on suitability and participant preference. If the head of the household is absent during the visit, the house will be marked on the map, and a second visit will be arranged for the next day. However, the house will be excluded if the head of the household is still not present during the second visit.

#### Data Analysis Procedure

The data analysis procedure will involve both descriptive and analytical analyses. Initially, a descriptive analysis will focus on the sociodemographic characteristics of the study population. We will examine the distribution of study variables by calculating frequency and percentage, along with reporting mean and SD. Since the outcome of interest is categorical, nonparametric tests will be used. Following the approach outlined in [26], responses categorized as inadequate and problematic will be grouped as inadequate (0), while those categorized as sufficient and excellent will be classified as adequate (1) during the analysis.

For the analytical analysis, we will carry out both bivariate and multivariate analyses to explore the determinants of health literacy among both the study population residing whining the PNP and the population living outside the PNP. This comparative approach will aim to determine which ecosystem has adequate health literacy. The significance level has been set to *P*<.05. The analytical analysis will be conducted using SPSS software (version 28.0, IBM Corp).

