#### Sample Size

Two approaches will be considered to calculate the optimal sample size (ie, using the odds ratio [OR] and prevalence). The selection will be based on the method producing the higher sample size. For the OR, the sample size will be calculated using the OR of health literacy in Malaysia [22], identified as 3.41 with a 95% CI. We will use the Open Epi Software (version 3.01) to calculate the sample size. With an OR of 3.41, the estimated sample size is 310 as shown in Table 2. Furthermore, Table 3 shows the comparison of sample sizes for exposed and nonexposed groups in Kelsey and Fleiss methods.

In contrast, the second method uses prevalence. In Malaysia, the health literacy prevalence among individuals aged 18 years and above is 35.5% [23]. Using this percentage, the minimum sample size calculated for this study is 323 people for a 95% CI. Since the prevalence sample size is higher than the OR, we decided to use it as our sample size. Considering a dropout probability of approximately 10%, the total sample size needed for this study is about 355 people. However, we will distribute a sample size of 400 people based on the ratio calculated. We estimate that out of 400 adults, approximately 200 households will need to be interviewed based on the assumption that 1 household has 2 adults. To ensure that the provinces within the national park are well represented, the percentage of the selected population is determined to be 24%, 64%, and 12% for Malay in Hulu Tembeling, Tembeling Tengah, and indigenous people, respectively. Using the stratified random sampling techniques, the number of samples allocated for each village is outlined in Table 1.

**Table 2 table2:** The estimated sample size.

Variables	Values, n
Sample size, n	310
Two-sided significance level (1-alpha)	95
Power (1-beta, % chance of detecting)	80
Ratio of sample size, unexposed/exposed	1
Percent of unexposed with outcome	5
Percent of exposed with outcome	15
Odds ratio	3.4
Risk/prevalence ratio	3
Risk/Prevalence difference	10

**Table 3 table3:** Comparison of sample sizes for exposed and nonexposed groups in Kelsey and Fleiss methods.

Variables	Kelsey (n=274), n (%)	Fleiss (n=272), n (%)	Fleiss with CC^a^ (n=310), n (%)
Sample size, exposed	137 (50)	136 (50)	155 (50)
Sample size, nonexposed	137 (50)	136 (50)	155 (50)

^a^CC: continuity correction.

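### The determinants analysis uses only a two-category version of health literacy; adding a model on the graded score or the four bands would recover a substantial part of the information

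*Protocol article*

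**What the plan says.** In the protocol article, Tools and Instruments (Table 4, Part 8) describes the HLS-SF-Q12 as 12 tasks rated on a four-point scale, "with a possible lowest mean score of 1 and a possible highest mean score of 4". The instrument is therefore graded.

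The Phase 3 Data Analysis Procedure gives the test family and its reason: "Since the outcome of interest is categorical, nonparametric tests will be used". It then fixes the coding, following a cited approach: "responses categorized as inadequate and problematic will be grouped as inadequate (0), while those categorized as sufficient and excellent will be classified as adequate (1". Bivariate and multivariate analyses of determinants follow. No model is named, and no analysis of the score or of the four ordered bands is mentioned. The stated purpose is binary: "This comparative approach will aim to determine which ecosystem has adequate health literacy". Data Entry and Analysis likewise takes health literacy status as the outcome.

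Both routes in Sample Size rest on a binary outcome. One uses an odds ratio ("identified as 3.41 with a 95% CI"), the other a proportion ("the health literacy prevalence among individuals aged 18 years and above is 35.5" percent). The final sample is 400 adults from about 200 households, assuming two adults per household.

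**The concern.** Objective 3 is to find factors associated with health literacy, and Phase 4 is to draw on the survey when interventions are chosen. The instrument records degrees of literacy, but the stated outcome coding keeps only which side of one cut a respondent falls on. A factor that moves people from the lowest band to the next, or from the third to the fourth, contributes nothing to a 0/1 outcome. The outcome is categorical because the plan makes it so, not because the questionnaire does.

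At stake is precision in the determinants analysis. For the same 400 interviews, associations will be estimated less precisely than the collected data allow, and some real but moderate ones may be missed. The article states the outcome coding and the test family, so this is a choice it makes and not a detail left to another document.

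**Working it through.** **1. The plan's own figure.** Sample Size states: "With an OR of 3.41, the estimated sample size is 310 as shown in Table 2". Inputs from Table 2: 5% with the outcome in the unexposed, equal groups, two-sided 5% level, 80% power.
- Odds in the exposed = 3.41 × 0.05/0.95 = 0.1795, so the proportion is 0.1795/1.1795 = 15.2% (15 in Table 2).
- The Fleiss formula gives 136 per group, 272 in all. With continuity correction it gives 155 per group, **310** in all.

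Both totals match Table 3. The study is sized on a two-category outcome.

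**2. Binary outcome against the full score.** The documents give no efficiency figure, so this step needs assumptions: a roughly normal score, and determinants that shift it without changing its spread. With a proportion p on one side of the cut, the large-sample relative efficiency is

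φ(z_p)² / [p(1 − p)],

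where z_p is the normal quantile at p and φ the normal density. The formula is the same for p and 1 − p, so it does not matter whether 35.5% is the share above or below the cut.

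At p = 0.355: z = −0.372, φ = 0.3723, so 0.1386/0.2290 = **0.605**, a loss of **39.5%**. In these terms 400 × 0.605 ≈ 242, so 400 binary responses carry the information of about 242 scores.

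| Split | Relative efficiency | Loss |
|---|---|---|
| 50% | 0.637 | 36% |
| 35.5% | 0.605 | 39.5% |
| 30% | 0.576 | 42% |
| 20% | 0.490 | 51% |
| 10% | 0.342 | 66% |

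The 10% row is the midpoint of the 5% and 15% in Table 2.

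**3. Cross-check by power.** Take 200 per group, an assumed difference of 0.28 SD and an average split of 35.5%. The binary proportions are then about 30.4% and 40.8%. Ignoring clustering, power is 80% on the score and 58% on the binary outcome. The totals needed for 80% power are 402 and 666, and 1 − 402/666 = 39.6%, in agreement with step 2.

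**4. Binary outcome against the four bands.** The recoding sentence merges four bands into two, so this is the loss from that step alone. The article gives no band shares, so they are assumed. Under the same normal model, the information in ordered bands relative to the full score is the sum over bands of (difference in φ between the two band limits)² / (band share).
- Shares of 25%, 39.5%, 25.5% and 10%: four bands 0.871, binary 0.605, ratio 0.695, loss 30.5%.
- Shares of 10%, 54.5%, 30.5% and 5%: four bands 0.829, binary 0.605, ratio 0.730, loss 27.0%.

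Five other sets of shares, with the main cut at 35.5%, 50% or 64.5%, fall between these two. The loss is about **27% to 31%**.

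**5. Power on the plan's own assumptions.** With 200 per group and 5% against 15%, the binary comparison has about 92% power.

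**The case against.** The strongest reply is that question, outcome and sample size agree. The protocol asks where literacy is adequate, which is a yes/no question. The grouping follows a cited approach, and both sample size routes assume a binary outcome. A reader might infer that dichotomising brings no gain, but the documents do not support that: the binary status gives an interpretable proportion, answers the stated question and allows comparison. This part of the reply stands.

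A reader might also infer that the study is underpowered because of the recoding. On Table 2's own assumptions it is not, as step 5 shows. That figure, however, concerns one contrast between equal, independent groups. It does not cover a multivariate search for factors among adults who share households.

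Two further inferences fail:
- **Nonparametric tests as a second fault.** Tests for categorical data follow from a categorical outcome and add no loss of their own.
- **Special harm to the Indigenous group.** Table 1 allocates 48 of 400 respondents to Indigenous villages, but the article states no separate analysis of them, and the relative loss in step 2 does not depend on group size.

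Finally, the article is a condensed account, its descriptive analyses may well show the score or the bands, and secondary models are often left to a fuller document. That is fair as far as it goes. It lowers the weight of the point but does not remove it, because the coding of the determinants outcome is stated and a more efficient companion analysis is available from the same data.

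**Conclusion.** The point holds as a low-cost improvement, not as an error. The stated determinants analysis rests only on the binary status although a graded score is collected. The loss against the score is about 36% to 42% for splits of 30% to 50%, with 39.5% at the protocol's 35.5%, and it grows as the split moves further from one half. Against the four ordered bands it is about 27% to 31%.

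These figures depend on a roughly normal score, shift-type effects and, for the last range, assumed band shares. The 35.5% is a national figure that may not hold in this population. None of the figures is given in the documents, so they should be read as conditional ranges. They do not show that the binary analysis is wrong, and they give no reason to drop it.

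**What to change.** In the Phase 3 Data Analysis Procedure:
- Keep the adequate/inadequate status for prevalence, for the question of which ecosystem has adequate literacy, and for comparability with the cited approach and the sample size basis.
- Add one prespecified determinants model on the HLS-SF-Q12 mean score, or an ordinal model on the four bands. Use a mixed model or generalised estimating equations with household as the cluster, and report it alongside the binary model (presumably logistic; the article names none).
- Limit the sentence that ties nonparametric tests to a categorical outcome so that it refers to the binary status only.

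The cost is one more model and one more results table, with no extra data collection. The drawback is interpretation: effects will be on a 1 to 4 scale for which the documents give no meaningful-difference threshold, or, for an ordinal model, will rest on its own assumptions across the bands. State in advance how the two models will be read together, so that disagreement between them does not leave a choice after the results are seen.

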**Objective:**

This study protocol examines the impact of the ecosystem on health literacy among rural communities in protected areas.

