### Phase 3: Identifying Health Literacy and Its Associated Factors in Rural Communities Surrounding Protected Areas

#### Participants and Sampling

This study will focus on the PNP. It covers 2477 square kilometers and was the country’s first national park established in Malaysia between 1938 and 1939, originally known as the King George V National Park. Following Malaysia's independence from British rule in 1957, the park was renamed. It is comprised of 3 protected areas in the states of Pahang, Kelantan, and Terengganu to form the central spine of Peninsular Malaysia. The national park has a reputation for being one of the world's oldest tropical rainforests, with an estimated age of 130 million years and a size of 4343 square kilometers.

Local communities in PNP are composed of Malay and Orang Asli (Batek and Semak Beri ethnicities). This location meets the criteria for this study because a protected area has been established and legal and other institutional measures have been established to promote them. The Pahang Department of Wildlife and National Parks (PERHILITAN) manages the PNP. The area is not open to the public except for those who have received prior approval from the authority for research purposes and minimal tourism activity at Kuala Tahan. Currently, the wildlife reserve contains a single research center that serves 2 distinct goals. The national park was originally established at Ulu Tembeling, with the first superintendent's office situated at Kuala Tahan. The southern section of PNP features a river boundary of over 80 kilometers along Sungai Tembeling, the Hulu Tembeling basin's principal river. Indigenous people inhabit the national park, while the Malay community resides near the river. For this study, respondents were drawn from the Malay and indigenous communities from the provinces of Hulu Tembeling and Tembeling Tengah. Table 1 shows the total number of respondents.

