### Strengths and Limitations

This study’s strength lies in its mixed methods analysis, employing a triangulation process to converge and validate both qualitative and quantitative data [27]. Moreover, this study will be conducted in multiple phases to discuss the issue comprehensively. This structured approach facilitates incremental progress [28]. Phases 1 and 2 are conceptual phases where the issue is identified and validated through a systematic review by stakeholders in PNP, such as government agencies, knowledge institutions, and civil society organizations. Phase 3 will design and plan the questionnaire and examine the health literacy status and its influencing factors among the community. The stakeholders in the FGD in phase 4 will validate the results of phases 1 to 3. Using these results, the stakeholders will discuss and design an effective health literacy intervention program. Finally, phase 5 will involve the dissemination of the health literacy intervention program to improve the health literacy status in the community. Moreover, a cost analysis will be calculated to analyze the cost of the program.

The study’s limitations became apparent during the FGD session with the stakeholders, as the invited participants did not attend. Consequently, we missed capturing unique macro-level perspectives. Another limitation is that the stakeholders’ views may not be representative of all who live inside or near the protected area in Malaysia or globally. Additionally, the study did not address the distinctions between locals and outsiders. Access to rural areas is difficult logistically, and the potential presence of wildlife, such as tigers, elephants, and bears, further complicates the research process.

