### Conclusions

In conclusion, this study will determine how different ecosystems, especially in protected areas, impact the health literacy of the local community using a mixed methods approach. The phases of the data collection process, incorporating both qualitative and quantitative methods, aim to comprehensively address the issue of health literacy in the local community. We will use these findings to disseminate a health intervention program, along with a cost structure, to improve health literacy among the protected area's community. The mixed methods study serves as a structured investigative model for evaluating and improving health literacy, health status, and well-being among all protected areas and communities worldwide.

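### Phase 3 promises an inside-versus-outside park comparison to say which ecosystem has adequate health literacy, but the sampling plan defines, allocates and sizes no outside group

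*Protocol article*

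**What the plan says.** **What is promised.** The Phase 3 Data Analysis Procedure says that bivariate and multivariate analyses will "explore the determinants of health literacy among both the study population residing whining the PNP and the population living outside the PNP" (the odd word is evidently a slip for within). It adds: "This comparative approach will aim to determine which ecosystem has adequate health literacy". The abstract's Objective reads "This study protocol examines the impact of the ecosystem on health literacy among rural communities in protected areas", Background and Conceptual Model repeats that framing, and the Conclusions say that "this study will determine how different ecosystems, especially in protected areas, impact the health literacy of the local community".

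**What is sampled.** The abstract's Methods place the survey in the PNP adult community, and Study Site names one protected area. Participants and Sampling says "This study will focus on the PNP" and that "respondents were drawn from the Malay and indigenous communities from the provinces of Hulu Tembeling and Tembeling Tengah". Table 1 lists 21 villages under a caption that names the PNP sample. The Sample Size section sets three strata: Malay in Hulu Tembeling (24%), Malay in Tembeling Tengah (64%) and indigenous people (12%).

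**The only hint of a location contrast** is one sentence in Participants and Sampling: "Indigenous people inhabit the national park, while the Malay community resides near the river".

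**The concern.** A comparison of two populations needs both to be defined, sampled and large enough. Here the analysis section names two populations and the sampling sections describe one site, with nothing that assigns a village or respondent to either side. An analysis plan cannot repair this, because what is missing is a feature of the sample.

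If the text stands, the analysts will have either no comparison to run or one improvised from whatever grouping is at hand. The most obvious grouping is indigenous against Malay. A difference in health literacy between those groups could then be published as an effect of the ecosystem, when it might reflect ethnicity, language, schooling or access to services. The survey results feed the Phase 4 intervention design, and the article offers the study as a model for other protected areas, so a misattributed difference would carry forward.

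**Working it through.** **1. Does any stratum represent an outside group?** Summing the sample column of Table 1:

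- Malay, Hulu Tembeling (5 villages): 15 + 22 + 25 + 11 + 22 = 95
- Malay, Tembeling Tengah (7 villages): 104 + 6 + 18 + 26 + 14 + 9 + 81 = 258
- Indigenous (9 villages, all in Tembeling Tengah): 6 + 10 + 13 + 3 + 6 + 2 + 3 + 3 + 2 = 48
- Total: 95 + 258 + 48 = 401, against the stated 400 (rounding)

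The household column sums to 603 + 1624 + 298 = 2525, giving 23.9%, 64.3% and 11.8%. This reproduces the stated 24%, 64% and 12%. The strata are fully accounted for by province and ethnicity. None is defined by position relative to the park.

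**2. Was the sample sized for such a comparison?** Two calculations are given.

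- *Odds ratio method.* With 5% in the unexposed and an odds ratio of 3.41, the exposed odds are 3.41 × 0.05/0.95 = 0.1795, so the exposed rate is 0.1795/1.1795 = 15.2%. At two-sided 5%, 80% power and 1:1, the Fleiss formula gives 136 per group (272). With continuity correction it gives 155 per group (310), which matches Table 3. The exposure is never identified as living inside or outside the park, and the method was set aside for the larger figure.
- *Prevalence method (adopted).* For one proportion, n = 1.96² × 0.355 × 0.645 / d². The margin d is not stated. Assuming d = 0.05, n = 352 for an unlimited population, or 329 with a finite correction for 5050 adults (2525 households × 2). The stated 323 is close to the latter. It is then raised by 10% (323 × 1.10 = 355) and rounded up to 400. This is a one-group precision calculation.

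Neither figure is a size for inside against outside.

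**3. What would the suggested split give?** Taking the text's sentence literally, indigenous villages are inside and Malay villages are by the river: 48 against 95 + 258 = 353, or 12% against 88%. On that reading all 9 indigenous villages fall on one side and all 12 Malay villages on the other, so location and ethnicity are the same variable and no model can separate them.

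For illustration, power = Φ[(|p1 − p2| − 1.96·SE0)/SE1], with SE0 pooled and SE1 unpooled. The assumption is 35.5% in the Malay group, and clustering is ignored:

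- 25.5% against 35.5%: (0.100 − 1.96 × 0.0730)/0.0679 = −0.64, power 26%
- 20.5% against 35.5%: (0.150 − 1.96 × 0.0727)/0.0636 = 0.12, power 55%

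**4. What if some Malay villages count as inside?** Participants and Sampling links limited tourism at Kuala Tahan with the park area. Kuala Tahan is a Malay village with 104 of the sample. Counting it as inside gives 48 + 104 = 152 against 401 − 152 = 249. Ethnicity then varies inside the park, but the outside group is still entirely Malay. The contrast within Malay respondents would be one village (104) against eleven (249), which cannot separate location from whatever else is particular to that village.

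**The case against.** The strongest reply is that an outside group may already be in the sample. No village in Table 1 is labelled inside or outside. Participants and Sampling describes the river as a park boundary and puts the Malay community near it. The numbered aims speak of communities around protected areas, and Anticipated Findings speaks of communities within and near PNP. Many of the 353 Malay respondents may therefore live beyond the boundary. The wording that ties Table 1 to PNP is a caption naming the study site, which is weak evidence that every village lies inside.

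This stands, and it rules out two stronger readings. A reader might infer that none of the 400 respondents lives outside the park; the documents do not establish that. A reader might also infer that location and ethnicity overlap completely; that rests on one general sentence, and Kuala Tahan may be an exception.

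The limitations sentence "Additionally, the study did not address the distinctions between locals and outsiders" should not carry weight either. Locals and outsiders are not defined there, and the sentence may mean native and incoming residents.

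A further fair point is that none of the five numbered aims in the Introduction is an ecosystem effect. The third concerns the level of health literacy and what is associated with it, and the adopted sample size serves that aim. The fault lies in two sentences of the analysis section and in the framing of the objective and conclusion.

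None of this supplies the missing definition. Possible outside residents do not make a comparison group until the plan says who they are.

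**Conclusion.** The contradiction holds in this form: the plan promises an inside-against-outside comparison and an ecosystem conclusion, while its sampling sections define, allocate and size no outside group. All 401 places in Table 1 are assigned by province and ethnicity. The only split the text suggests (48 against 353) would coincide with ethnicity.

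How far location and ethnicity really overlap is unknown, because village positions are not stated. The conclusion does not depend on the answer: with one site and no defined comparison population, an ecosystem effect cannot be separated from ethnicity and other differences between villages. The power figures are illustrative, rest on an assumed 35.5% in the Malay group, and are optimistic because they ignore household and village clustering.

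The survey, the prevalence estimate and the associated-factors analysis stand. The ecosystem claim does not, and it should be corrected before results are reported.

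**What to change.** - In the Phase 3 Data Analysis Procedure, delete the inside/outside comparison and the sentence about which ecosystem has adequate health literacy.
- In the Objective, Background and Conceptual Model, and Conclusions, replace the impact-of-ecosystem wording with the third numbered aim: to estimate the level of health literacy, and the factors associated with it, in communities in and around PNP.
- If a location question is kept, classify the existing 21 villages by position relative to the park boundary, or by distance from it, before analysis. Fit that variable with ethnicity in the model, or within the 12 Malay villages only (353 respondents), and report the result as an association. Location is a village-level variable, so the number of villages limits what it can show.

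The cost is revised wording in a few places and, if the location question is kept, one recorded value per village. The downside is a more modest claim.

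Keeping the comparison as promised would cost far more. It would need a defined outside population with its own sample. As an illustration, to detect a 10-point difference from 35.5% (1:1, two-sided 5%, 80% power, no continuity correction or clustering allowance), 332 to 378 per group are needed. With 10% dropout that becomes 332/0.9 = 369 to 378/0.9 = 420 per group. Even then, one park against one outside area would support only an association.
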